### 1. Aims/objectives/research question/hypotheses:

The aim of the study is to determine the effectiveness of a psychotherapeutic intervention – namely, Components-Based Intervention (CBI) – in reducing the severity of mental health symptoms experienced by torture and violence survivors displaced from Burma into Thailand. Specifically, the intervention seeks to measure reductions (if any) in symptoms of depression and trauma. These two problems were prominently identified in the qualitative research (IRB#3047) that preceded this intervention evaluation phase of the project. Depression symptoms will be measured using a modified, locally validated version of the Hopkins Symptoms Checklist (HSCL) and trauma exposure and symptoms will be measured using a modified, locally validated version of the Harvard Trauma Questionnaire (HTQ). The study seeks to compare the effect of the CBI intervention against no CBI intervention. We are not comparing the CBI intervention with other available services and treatments, which may include non-specific counseling services and/or inpatient care. While the study does not discourage any use of standard of care treatments, and will document any such services (including possible medication) in the client monitoring records, we do not make any hypotheses about what effects the presence or absence of other treatments would have on study results.

### 2. Background and rationale:

Little is known about the effectiveness of most mental health interventions among torture survivors. Interventions provided to survivors are usually based on limited evidence because few studies have specifically targeted survivors. This has led to controversy in the field of torture treatment between those who believe that the rationale for current treatments is appropriate and those who believe that torture survivors present a unique set of challenges that may render such treatments unsuitable. The few studies that have been done were mostly among torture survivors living in developed countries. They therefore face different challenges than those living in low resource environments and in the countries in which the torture occurred. In the case of the Southeast Asia—in particular the situation of Burmese populations experiencing torture and systematic violence—we know of no completed studies of treatments for torture survivors and therefore have no scientific evidence as to which interventions are acceptable to local people, which are feasible given local resources, and which are effective given the local culture and the other challenges in the lives of survivors. Therefore, in this study we are evaluating a psychotherapeutic intervention—namely, Components-Based Intervention (CBI)—to treat the mental health problems of torture survivors, drawing upon preliminary results from Johns Hopkins University (JHU) studies in Northern Iraq (IRB#2091), Southern Iraq (IRB #3034), and in consideration of the mental health problems described by displaced Burmese populations in previous JHU research on the Thailand-Burma border (IRB #3047, IRB#3348).

The study is part of an award by the USAID Victims of Torture Fund (USAID/VTF) to JHU to work with local and international organizations serving survivors of torture and systematic violence. For this study, the intent is to assist in the design, implementation, monitoring, and evaluation of programming to understand and address the psychosocial needs of Burmese displaced across the Thai/Burma border who are living in the area of Mae Sot, Tak Province in Thailand. Specifically this project involves collaboration with the Burma Border Project (BBP), the Mae Tao Clinic (MTC),

the Assistance Association for Political Prisoners (AAPP), and Social Action for Women (SAW), to help improve the quality and effectiveness of psychosocial and mental health programs.

The Components-Based Intervention includes psycho-education, relaxation, life-enhancing skills (problems solving and safety planning), family support, and cognitive processing of life problems and traumatic events. The CBI model is being tested in a JHU study in Southern Iraq and preliminary results suggest that it may be effective for the population of displaced Burmese in Thailand. The duration of sessions is one hour, the frequency of treatment is weekly, and the recommended number of sessions in the Thailand/Burma border site is 10.

In February-March 2011, US-based clinical psychologists trained 20 counselors and 4 supervisors in CBI techniques. The training curriculum involved 10 full days (8:00am – 4:00pm) of live training including didactic explanations, demonstration role-plays and small-group role-plays. CBI components covered in the training included:

- 1) Pre-Treatment (consent, intake/screening, and assessment)
- 2) Encouraging Participation (why mental health services are important)
- 3) Psychoeducation (information about problems and treatment process)
- 4) Behavioral Coping Skills: Relaxation (helping clients learn ways to cope with stress)
- 5) Behavioral Coping Skills: Behavioral Activation (helping clients to do activities they enjoy)
- 6) Cognitive Coping (counselors talk with clients about how thoughts, feelings and behavior are connected and how to think in different ways in order to change feelings and actions)
- 7) Gradual Exposure (for Trauma) (counselor engages client in a direct detailed discussion about traumatic events he/she has experienced and connected thoughts and feelings)
- 8) Live Exposure (for Fear-based Anxiety) (counselors talk with clients about slowly, step-by-step, facing a place/thing they are afraid of)
- 9) Cognitive Reprocessing (counselors challenge client's unhelpful and inaccurate thoughts)
- 10) Enhancing Safety (counselors ask clients specific questions about safety and suicidal ideation and work with client to develop and implement a safety plan)

Starting in June 2011, the counselors trained in CBI will begin to implement this intervention with the clients that come to see them as part of the ongoing services provided by AAPP, SAW, and MTC. A practicum round of the CBI intervention began shortly following the CBI training in order to be sure that counselors and supervisors are properly trained in the intervention. The research study will begin in June 2011 when approximately 400 people will be screened into the intervention (for a final sample of 300); approximately half of these would be randomly assigned to the “case” group, to begin the intervention immediately after screening while the other half would be assigned to the “wait-control” group to receive CBI after the “case” group has completed the CBI intervention.

The proposed study will be embedded within the ongoing MTC, SAW and AAPP programs which could include non-specific counseling services, social services and support and, in the case of Mae Tao clinic, medical assistance. That is, we are proposing to study the effectiveness of these intervention strategies in a subset of the clients the organizations serve. The organizations will continue to provide services, as space allows, to anyone who seeks their services regardless of whether they meet eligibility for our proposed study. However, those who meet our inclusion criteria will be invited to participate in the research component of the service program.

### **3. Participants:**

Persons eligible for participation in this study will include the following: adults from Burma (18 and older) living in Mae Sot with significant mental health problems; who were affected by torture and systematic violence (that is either directly subjected to torture and imprisonment, or indirectly

through witnessing torture, or who are a close family member of a survivor) and who are not actively suicidal. Eligible persons will mainly be located with the assistance of our local organizational counterparts. Some may be former prisoners who were tortured in prison by the Burmese military regime. Others will be identified as they present to the local organizations seeking help for various problems, including mental or physical disorders. All those who are found to be eligible will be invited to join the trial.

Screening will be done using an instrument developed for use among this population (see attached document). For the baseline interview, Section 1 (Demographic Characteristics), Section 2 (Trauma Events), Section 3 (Depression Symptoms) and Section 4 (Trauma Symptoms) will serve as the screening tool to identify persons found to have experienced or witnessed torture or systematic violence and who exhibit significant symptoms of trauma or depression. This will comprise Part A: Screening Instrument of the baseline interview.

Those who are found to be eligible on exposure and symptoms criteria—and who are also eligible by being adults from Burma living in Mae Sot, Thailand—will be consented to continue the full intake/assessment interview and to join the trial. Part B of instrument comprises the intake/assessment portion, and includes Section 5 (Anxiety), Section 6 (Function Assessment), Section 7 (Current Problems), Section 8 (Aggressive Behavior) and Section 9 (Alcohol Use).

There may be some individuals who are deemed eligible and have consented to participate in the study but who, following the full intake interview, would be deemed excludable either because they are a danger to themselves or others, or who are psychotic or otherwise deemed not competent to give consent or participate in the interventions. While we believe the study intervention is not appropriate for these individuals, counselors will review the cases with their clinical supervisors and the JHU study team to ensure that every effort is made to provide these individuals with referral to appropriate care.

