### 5) *A brief data analysis plan and description of the nature of the variables to be derived*

As noted previously, depression and trauma were the two mental health problems that were prominently identified in the qualitative research (IRB#3047) that preceded this intervention evaluation phase of the project. Depression symptoms will be measured using a modified, locally validated version of the Hopkins Symptoms Checklist (HSCL) and trauma exposure and symptoms will be measured using a modified, locally validated version of the Harvard Trauma Questionnaire (HTQ). The data generated from the validation study has been used to develop depression and trauma scale cutoff scores for the study population. The counselors will calculate the total score for these subscales during the initial screening interview, since scores on either of these scales above the cutoffs are part of the eligibility criteria (13 or above for

depression symptoms and 45 or above for trauma symptoms). Following randomization into a case group and a wait-control group, the counselors will provide the intervention to the case group. At the end of the intervention, the case group and the wait-control group will be re-interviewed using the same instrument employed in the screening interview. The mean change in the various subscales between pre and post intervention interviews will be calculated and subtracted from the mean change (calculated in the same way) for the wait-control group. The differences will be the amount of change on each scale due to the intervention.

In terms of statistical analysis, we will keep the data on study participants in the intervention group who get other standard of care treatment or participants in the wait-control group who need immediate treatment. All study participants who meet screening criteria for eligibility and enroll in the study will be included in the analysis on an intent to treat basis.

6) *If human biospecimens (blood, urine, saliva, etc.) will be collected, provide details about collection, volume (ml) or number, use, storage, identification, and disposal.*

Not Applicable

7) *Describe how subjects will be screened for eligibility and assigned to study/intervention and comparison/control groups.*

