Measures of trauma or depression symptoms will be based on the responses to all trauma and depression questions in the screening interview. The counselors will calculate the total score for these questions (defined as the total trauma and depression subscales) while the interviewee is still present. If this meets or exceeds a cutoff score of 45 for trauma---reflecting likely clinically significant symptoms (based on results of a previous validity study of the instrument among the same population) and/or a cutoff score for depression of 13 or more ---reflecting likely clinical significant depression (again based on results of the previous validity study)---then the person will be invited to join the trial after having been read a consent form which explains the trial. If they agree they will be assigned either to receive treatment beginning soon or be told that they are on a wait-list and will need to wait several months before receiving treatment. If they are eligible but decline to participate in the trial, the counselor and clinical supervisor, in consultation with the JHU study team, will review treatment options on a case-by-case basis. Depending on the outcome of this assessment, these individuals could be offered to receive the study treatment (though not participate in the study) or they could be referred to other appropriate programs and services in the Mae Sot area.

While the study imposes no upper cut-off point for depression and trauma symptoms (and thus would not exclude persons with acute mental illness), there may be some individuals who are deemed eligible and have consented to participate in the study but who would be excludable either because they are a danger to themselves or others, or who are psychotic or otherwise deemed not competent to give consent or participate in the interventions. While we believe the study intervention is not appropriate for these individuals, counselors will review the cases with their clinical supervisors and the JHU study team to ensure that every effort is made to provide these individuals with referral to appropriate care.

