In the case of individuals who evidence signs of active suicidal ideation, counselors and clinical supervisors have been trained on suicide assessment as part of their CBI training. In all cases involving potential danger of a client harming him/herself or others, counselors will follow the study Safety Plan to request assistance in assessing the need of follow-up care and services for that individual. On a case-by-case basis, the study team will work with the counselor and clinical supervisor, along with [name] and the study team's clinical experts, to determine whether to offer the individual the study treatment (if they are excludable from the study intervention), or the study intervention (if they are otherwise eligible and no longer deemed an active risk to harm themselves or others), or some other available and appropriate treatment.

*Randomization process:*

If the subject is deemed eligible and consents to join the trial, the subject will be randomly allocated to the case group to receive treatment immediately or to the wait-control group. The randomization process will be as follows:

1. Each counselor will receive a list of participant ID numbers in sequence (i.e. 1-15) which have been randomly allocated to either intervention or wait-control via a random number generator, with a 1 to 1 ratio of intervention to wait-list. There will be one list for each counselor. Counselors will not be aware how numbers have been allocated.
2. For each counselor, a paper indicating the treatment assignment (intervention or wait-list) will be folded and stapled directly to the back of consent forms that are pre-numbered with a client ID number.
3. Once the subject has consented to be in the study, the counselor will assign a number to the client in the order in which they are recruited. They will remove and unfold the paper attached to the form that corresponds to their ID number, and will inform the subject whether they will begin the intervention immediately or will be put on the wait list.

The study investigators will keep master lists for each counselor which indicate the allocated group status (intervention or wait-control) for each client ID number to ensure fidelity to the randomization model.

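### No sentence requires the full intake and exclusion review to be finished before the allocation paper is unfolded, so exclusion can be judged with the arm known

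*Protocol*

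**What the plan says.** Section 3 divides the baseline instrument in two. Part A (Sections 1 to 4: demographics, trauma events, depression and trauma symptoms) is the screening tool. Part B (Sections 5 to 9: anxiety, function, current problems, aggressive behavior, alcohol use) is the full intake. One study consent is taken after Part A, and it covers both Part B and joining the trial. The section then provides for people "deemed eligible and have consented to participate in the study but who, following the full intake interview, would be deemed excludable" on grounds of danger, psychosis or lack of competence.

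Section 4, item 7 repeats this provision for individuals "who are deemed eligible and have consented to participate in the study but who would be excludable either because they are a danger", or on the other grounds, without saying when the decision is made.

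On allocation, the same item says:
- "If they agree they will be assigned either to receive treatment beginning soon or be told that they are on a wait-list";
- "If the subject is deemed eligible and consents to join the trial, the subject will be randomly allocated to the case group" or to the wait-control group;
- the assignment paper "will be folded and stapled directly to the back of consent forms that are pre-numbered with a client ID number" (step 2);
- "Once the subject has consented to be in the study, the counselor will assign a number to the client" in order of recruitment, and then "They will remove and unfold the paper attached to the form that corresponds to their ID number" and tell the subject the result (step 3).

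Section 4, item 5 puts in the analysis all participants "who meet screening criteria for eligibility and enroll in the study will be included in the analysis on an intent to treat basis".

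**The concern.** The people described as excludable have already met the two conditions on which item 7 allocates: they are eligible and they have consented. If the counselor opens the paper at consent and then conducts Part B, both counselor and participant know the arm when a reason for exclusion comes up. The counselor also takes part in the exclusion review.

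Knowing the arm could affect the judgment. For a person with active suicidal ideation who is excludable, one option listed in item 7 is to offer the study treatment anyway. For someone just told to wait, exclusion could then look like a way to earlier care. For someone in the case group, the counselor would be judging a person they are about to treat. Supervisors and the study team share the decision, which limits the risk, but nothing says that they are unaware of the arm. Keeping counselors ignorant of the list protects concealment only until the paper is opened.

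What is at stake is the comparability of the arms. If exclusions depended on the arm and those people were left out of the analysis, the groups compared would no longer be the groups formed at random.

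**Working it through.** The point is about the order of events and rests on no figure in the protocol, so there is no figure to reproduce.

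**Order of events, taken literally**

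1. Part A is scored and the person meets the exposure and symptom criteria (section 3; section 4, item 7).
2. Study consent is taken. It covers Part B and trial entry together, so it comes before Part B (section 3).
3. The trigger for numbering and unfolding is consent (section 4, item 7, step 3). Part B is not named as a condition. The paper is stapled to the consent form, so it is in the counselor's hands at that moment.
4. Exclusion for danger, psychosis or incompetence follows the full intake (section 3) or has no stated time (section 4, item 7).

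Step 3 may therefore come before Part B and step 4. No sentence requires that order, and none forbids it.

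**Which exclusions are exposed**

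- Active suicidality is largely covered: its absence is an entry criterion in section 3.
- Clear incapacity is covered: section 7a says such a person would not be asked to join.
- Psychosis or danger to others that emerges during Part B is not covered. The aggressive-behavior section of the instrument is in Part B.

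**Scale, under assumptions that are not in the protocol**

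Let a share q of one arm be excluded and left out of the analysis, and let their mean change differ from that of the rest by D standard deviations (SD). The full arm mean is (1 − q)·m + q·(m + D) = m + q·D. Without them it is m, so the shift is q·D. Equal shifts in both arms cancel, so only a difference between arms matters. With 150 per arm (section 4, item 14), no exclusions in the other arm, and a planned effect of 0.50 SD:

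| q | People of 150 | Shift for D = 0.5 | Shift for D = 1.0 | Share of 0.50 |
|---|---|---|---|---|
| 2% | 3 | 0.01 SD | 0.02 SD | 2% to 4% |
| 5% | 7.5 | 0.025 SD | 0.05 SD | 5% to 10% |
| 10% | 15 | 0.05 SD | 0.10 SD | 10% to 20% |

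Both q and D are assumed. The lower rows need a large one-sided exclusion that nothing in the protocol predicts.

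**The case against.** The best reply is that the safe order is already implied. In section 4, item 7, the paragraph on suicidal ideation stands directly before the randomization steps and treats the absence of active risk as a condition for being offered the study intervention. The general exclusion paragraph also comes before those steps. Section 7a lists intake ahead of randomization when it describes what the study consent offers. Consent can be read as a necessary condition for unfolding the paper, not as an instruction to do so at once, and a folded paper can stay folded through Part B.

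Most of this stands as evidence of intent. It is not a rule. The list in section 7a gives the content of an offer, and paragraph order does not tell twenty counselors what to finish first. The step they will carry out names consent only.

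A reader might infer three stronger things that the protocol does not support.
- *That the paper is meant to be opened before intake.* No sentence says so.
- *That people excluded after allocation are dropped from the analysis, or that their status is open.* The inclusion sentence in section 4, item 5 refers to screening criteria, and screening is Part A. Someone found excludable after Part B has met those criteria and has consented, so the plain reading keeps them.
- *That the rule disenrolling people who miss Session 1 (section 7a) is part of this problem.* It concerns attendance after allocation and should be handled as a separate point.

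**Conclusion.** The concern holds as a gap in the stated sequence. The paper's opening is tied to consent, exclusion comes after consent and after Part B, and nothing requires the exclusion decision to come first. Followed literally, the procedure lets the counselor know the arm when exclusion is raised.

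The size of any bias cannot be given, because the protocol states no exclusion rate and no direction in which judgments would differ. It is probably small: the grounds are narrow, the review is shared, the master lists make opened papers traceable, and the plain reading of the intent-to-treat sentence keeps allocated people in. Bias in the comparison would need three things together: papers opened before Part B, exclusions that differ by arm, and those people missing from the analysis. The change is worth making because the protection is nearly free, not because harm to the result has been shown.

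**What to change.** **Section 4, item 7, step 3.** State that the number may be assigned at consent but the paper stays folded until Part B and any exclusion review are complete and the decision is recorded. If the person is excluded, the unopened number is voided and then logged on the master list. An unopened paper tells the counselor nothing, so voiding it introduces no bias, and no temporary numbering or separate consent form is needed.

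**Section 4, item 5.** Add that anyone whose paper has been opened stays in the intent-to-treat analysis in the allocated arm, including anyone found excludable later. This confirms the plain reading. Changing or stopping such a person's treatment for safety is unaffected.

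**Cost.** Two or three sentences, a line in the counselors' consent training, and a short delay in allocation for the few people who need review. Section 4, item 2 already has suicide danger discussed with supervisors at once. Other cases could wait about a week, if they are held for the weekly supervision meeting and that schedule also runs during intake.
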